#### Procedure

The new procedure consists of the application of a formula, in either liquid or spray, which contains 95% extra virgin olive oil. This product will have the same appearance as the hyperoxygenated fatty acid, using the same presentation, which will make it appear identical to both patients and nurses. This intervention will be applied to both groups (control and target group). Both the patients of the control group and those patients who are part of the target group will receive the preventative instructions stated in the clinical practice guidelines on deterioration of skin integrity issued by the Health District of Malaga. For such purposes, the caregivers of both groups will be trained in the mentioned procedures. In addition to these preventative measures, the patients included in the control group will receive two applications per day of the HOFA-based product in the skin, more specifically, in the sacral area, the hips, and the heels. For the purpose of this trial, we will use a HOFA product bearing the CE marking, IIb Class, with a higher classification than other products existing in the market. The product is to be applied topically and includes hyperoxygenated fatty acids, *Equisetum Arvense*, *Hypericum Perforatum*, and perfume. On their part, the target group will receive, as well as the preventative measures mentioned above, two daily applications of the olive-oil-based formula in the skin areas of sacrum, hips, and heels. The appearance of pressure ulcers will be registered in the weekly follow-up report, which will include an assessment of whether the skin integrity is maintained or not. In the event that there is any adverse effect during the follow-up period, the research group will be informed and such events will be notified by means of a specific document designed for such purposes.

#### Statistical analysis

Initially, a descriptive analysis of the variables included in the trial will be performed. Continuous variables will be summarized with mean, standard deviation, median, and interquartile range. Categorical variables will be shown in absolute and relative frequencies. An analysis of the normal distribution by the Kolmogorov-Smirnov test, symmetry analysis, and kurtosis will be performed.

With the aim of assessing the noninferiority of the olive oil for the prevention of pressure ulcers, a contrast of association between the appearance of pressure ulcers and the kind of treatment received (olive-oil-based cream or conventional treatment) will be carried out, by absolute and relative measures of effect sizes (complete reduction of risk, number needed to treat, relative risk, and relative reduction of risk), with their respective confidence intervals at 95%. It will be determined whether the confidence interval includes the estimated delta value from the sample or not, so as to reject or accept the null hypothesis.

A bivariate analysis will be carried out using the Student’s t and chi-squared tests according to the characteristics of the variables analyzed in the event that these are normally distributed. Otherwise, nonparametric tests will be applied, such as the Wilcoxon and Man-Whitney U tests. Likewise, analysis of variance (ANOVA) will be applied for the association of quantitative and qualitative variables in the necessary cases, as well as robust measures of central tendency in cases of homoscedasticity (which will be tested by Levene’s test) by means of the Welch and Brown-Forsythe test.

An analysis according to the Kaplan-Meier curves and log-rank test will be carried out to determine the progress of the appearance of pressure ulcers in both groups, taking into account the treatment applied, the sex, age, nutritional status, and functional degree of the patient and the caregiver’s age.

For the analysis on cost-effectiveness, the effectiveness measures previously established (*U*_1_ and *U*_0_) will be obtained. The increase in cost for each option (Δ*C*_*ij*_) will be estimated, as well as the increase of effectiveness rate, when comparing the two options, the cost-efficiency ratio of each treatment and the incremental cost-effectiveness ratio of each option. These values will enable us to assess the necessary cost to increase by 1% the possibilities of success when preventing pressure ulcers in these patients by using each product.

The analysis will be carried out according to the protocol, as established for the noninferiority studies, to ensure the difference conditions between the treatments and increase the rejection conditions of the null hypothesis. Nevertheless, an analysis will be carried out that is intended to compare both analyses and assess, if the analyses differ, the subgroups of patients who did not comply with the trial protocol with the aim of identifying the possible reasons for the withdrawal from the trial, before accepting or rejecting the null hypothesis. The confidence intervals of the main result variable will be analyzed to determine whether the difference found is within the bound established for the delta value. Statistical analysis will be performed using SSPS 20 software.

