**Methods/design:**

The main objective is to assess the effectiveness of olive oil, comparing it with HOFA, to treat immobilized patients at home who are at risk of pressure ulcers. As a secondary objective, the cost-effectiveness balance of this new application with regard to the HOFA will be assessed. The study is designed as a noninferiority, triple-blinded, parallel, multi-center, randomized clinical trial. The scope of the study is the population attending primary health centers in Andalucía (Spain) in the regional areas of Malaga, Granada, Seville, and Cadiz. Immobilized patients at risk of pressure ulcers will be targeted. The target group will be treated by application of an olive-oil-based formula whereas the control group will be treated by application of HOFA to the control group. The follow-up period will be 16 weeks. The main variable will be the presence of pressure ulcers in the patient. Secondary variables include sociodemographic and clinical information, caregiver information, and whether technical support exists. Statistical analysis will include the Kolmogorov-Smirnov test, symmetry and kurtosis analysis, bivariate analysis using the Student’s t and chi-squared tests as well as the Wilcoxon and the Man-Whitney U tests, ANOVA and multivariate logistic regression analysis.

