## Methods/design

The design of this study is a noninferiority, triple-blinded, parallel, multi-center, randomized clinical trial. The blinded groups are the patients and their caregivers, nurses and the research group.

The null hypothesis of this study is that the difference in the appearance of pressure ulcers in immobilized patients at home who receive olive oil (*G*_o_), in contrast to those patients applying HOFA (*G*_h_) is higher than the delta value established at 10% (*H*_0_ = *G*_o_ − *G*_h_ > 10%), that is to say, that the lower bound of the confidence intervals includes that 10%. In the event that it is possible to reject the null hypothesis, the alternative hypothesis of this study will be that olive oil is not lower than 10%, compared with the HOFA (*H*_1_ = *G*_o_ − *G*_h_ < 10%); in other words, the lower bound of the confidence interval of the difference between both products is lower than 10%.

Two procedures will be performed: usual care and application of HOFA to the control group and usual care and application of an olive-oil composition to the target group. The main outcome will be the appearance of grade 2 pressure ulcers. The accuracy of the trial with regard to the control medicine (HOFA) is widely supported, owing to the favorable historical results of such medicine against placebo [25] as per recommendations of the International Conference of Harmonization and also because the efficiency conditions of the mentioned medicine will be met for the purpose of this trial.

The target population will be patients included in the immobilized-patients program within the nursing care at home service provided in Health Centers in Andalucía (Spain), and more specifically in the regions of Malaga, Granada, Seville, and Cadiz.

The inclusion criteria will be: patients over 18 years; not having pressure ulcers; patients supported by a family or a remunerated caregiver for the application of the treatment; diagnosed by a nurse as a ‘risk for impaired skin integrity’, by applying the Braden Scale for prediction of pressure ulcer risk, showing a high risk (score ≤ 12) or moderated risk (score 13 to 16), and; patients with nutritional status assessed according to the Mini Nutritional Assessment scale scoring 10 or less.

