### Sample selection

The directors and care service coordinators of each health center will be duly informed about the trial, and they will be asked for their availability as well as their consent to take part in the trial. Nursing staff of each health center who so desire will be able to take part, being in such case responsible for the research study implementation and follow-up in their respective health center.

Records of patients included in the nursing at home program for immobilized patients will be assessed to determine whether patients comply with the inclusion requirements. At this point, such patients will sign the informed consent form and subsequently, their details will be randomized by a computer system independent of the professional staff, which will be processed at the clinical trial control center.

To achieve a power rate of 80.00% to reject the null hypothesis (*H*_0_: the difference between proportions *p*1 and *p*2 is lower than the noninferiority bound), using a normal asymptotic analysis test (noninferiority), unilateral proportions for two independent samples, taking into account that the level of statistical significance is 5.00%, and assuming that the proportion in the reference (control) group is 45.00% and the proportion in the experimental group is 45.00% [9], the proportion of experimental units in the reference group is 50% related to the total and the noninferiority bound (delta) is 10.00%, then, it will be necessary to include 306 experimental units in the reference group and 306 units in the experimental group, totalling 612 units in the study. Taking into account that the expected withdrawal rate is 15.00%, it will be necessary to enroll 360 experimental units in the reference group and 360 units in the experimental group, totalling 720 experimental units in the trial.

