## Discussion

Pressure ulcers are nowadays considered an important health issue causing a great economic impact by substantially increasing pharmaceutical expenditure. The total expenditure of pressure ulcer treatments amounts to 5% of annual health care expenditure and causes a higher health care burden on professional staff. This is a public health problem, which affects mainly older people, thus, this disease rate is increasing.

The acceptance of our hypothesis will provide evidence supporting the regular use of olive oil (nonoxygenated fatty acids) in the prevention of pressure ulcers in primary health care, likewise involving hospital care. Furthermore, owing to the lower price of the product, primary health care districts may consider purchasing them, owing to the reduction in health care workload for professional staff, as well as for the family caregivers, given that the incidence of pressure ulcers will be lower as well as the respective reduction in pharmaceutical expenditure.

The main limitation of the trial is that when performing the cost-effectiveness analysis, the variables on caregiver inputs may not be estimated, along with those variables regarding the expenditure derived from the patient’s suffering. Likewise, there might be a selection bias due to those patients who refuse to take part in the trial, which may involve differential baseline characteristics. For the purposes of this trial, in the analysis it will be taken into account whether there are differences among those who take part in the trial and those who do not. The same procedure will be applied for withdrawals during the follow-up period. The analysis will be carried out according to the protocol and intention to treat. In the event that the results of the two types of analysis do not match, the subgroup of patients who did not comply with the protocol will be studied, to determine the reasons before reaching a final conclusion of noninferiority.

The confusion bias derived from some variables such as age, sex, type of intervention, and nutritional status of the patient will be managed during the statistical analysis stage, by means of a multivariate analysis.

The usual application of olive-oil-based formulas may be helpful in preventing the appearance of any grade of pressure ulcer in immobilized patients, and thus, it will be a cheaper treatment and may be considered as an alternative treatment.

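### The noninferiority contrast uses no baseline covariates, and the planned multivariate model is not tied to the 10-point margin, so recorded predictors of ulcer risk do not sharpen the decision

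*Protocol article*

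**What the plan says.** The Statistical analysis section describes the noninferiority comparison as "a contrast of association between the appearance of pressure ulcers and the kind of treatment received". It is reported as absolute and relative risk measures with 95% confidence intervals. The hypotheses in Methods/design, the Sample selection section and the end of the Statistical analysis section all place the decision on a difference in proportions against 10 percentage points.

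Adjustment is mentioned separately:
- The abstract's list of methods ends with "ANOVA and multivariate logistic regression analysis".
- The Discussion says that "The confusion bias derived from some variables such as age, sex, type of intervention, and nutritional status of the patient" will be handled by a multivariate analysis.
- The Kaplan-Meier and log-rank analyses are to take account of sex, age, nutritional status, functional degree and the caregiver's age.

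None of these is linked to the 10-point margin.

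Baseline risk is recorded on every patient. Eligibility is judged "by applying the Braden Scale for prediction of pressure ulcer risk" and by a Mini Nutritional Assessment score. The Sample selection section also lists information on previous ulcers, comorbidity, incontinence and support equipment among the patient variables.

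**The concern.** Noninferiority is decided by whether a confidence limit for the risk difference stays below 10 points. The width of that interval therefore determines the chance of a conclusive result. If baseline factors predict who develops an ulcer, an estimate that adjusts for them has a smaller standard error for the same patients. It also corrects for chance imbalance in those factors.

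As described, the plan does not use this gain. The primary contrast has no covariates. The usual direct output of a logistic model is an odds ratio, which is on a different scale from the margin. The article describes no step that would turn the model into an adjusted risk difference. At stake are a few points of power and a well-defined adjusted companion to the primary result.

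**Working it through.** **Inputs from the Sample selection section.** The test is described as "unilateral proportions for two independent samples", "the level of statistical significance is 5.00" per cent, with the aim "To achieve a power rate of 80.00% to reject the null hypothesis". The planned risks are given as "assuming that the proportion in the reference (control) group is 45.00% and the proportion in the experimental group is 45.00" per cent. The margin is 10 points, allocation is equal, and withdrawal is 15%.

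**Step 1: reproduce the plan's figures.** The unadjusted two-proportion formula is

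n per arm = 2p(1−p)(z₀.₉₅ + z₀.₈₀)² / δ² = 0.495 × (1.645 + 0.842)² / 0.01 ≈ 306.04.

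The article states 306 (307 if rounded up). With withdrawal, 306 / 0.85 = 360, as stated. The sample size and the crude contrast therefore agree.

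**Step 2: precision and power of the crude difference at 306 per arm.** SE = √(0.495 / 306) = 0.0402, or 4.02 points. Power = Φ(0.10 / 0.0402 − 1.645) = 80.0%.

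**Step 3: the same with covariate standardisation.** The variance is multiplied by (1 − R²), where R² is the share of outcome variance explained by the baseline covariates: SE_adj = √(0.495(1 − R²) / 306). The article gives no value for R², so a range is shown.

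| Assumed R² | SE (points) | Power at 306 per arm, one-sided 5% | Evaluable n per arm for 80% power |
|---|---|---|---|
| 0 | 4.02 | 80.0% | 307 |
| 0.05 | 3.92 | about 82% | 291 |
| 0.10 | 3.82 | about 84% | 276 |
| 0.20 | 3.60 | about 87% | 245 |

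To give R² a meaning: if half the patients had a 60% ulcer risk and half a 30% risk (an illustration, not a figure from the article), R² = 0.15² / (0.45 × 0.55) = 0.0225 / 0.2475 = 0.09.

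**Step 4: check by simulation.** A logistic model with one baseline prognostic score was fitted with 306 per arm, 45% risk in both arms and 1,500 runs per setting. It was then averaged into a risk difference. At R² of about 0.06, 0.11, 0.17 and 0.23, the variance was 0.94, 0.89, 0.83 and 0.80 of the crude variance. At R² of about 0.11, power at one-sided 5% rose from 82% to 86% (Monte Carlo error about 1 point). With R² = 0, nothing was gained or lost beyond that error.

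**Step 5: scale.** Ten points above a 45% control risk is an odds ratio of (0.55/0.45) / (0.45/0.55) = 1.49. Above 20% it is (0.30/0.70) / (0.20/0.80) = 1.71. Above 10% it is (0.20/0.80) / (0.10/0.90) = 2.25. A raw odds ratio thus has no fixed reading against the margin. The averaged predicted risks from the same model do.

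**The case against.** The strongest reply is that nothing here is wrong. Margin, estimate and sample size share one scale. A crude risk difference in a randomised comparison is valid and does not inflate the type I error. Chance imbalance is already allowed for in its confidence interval. A condensed article commonly leaves the covariate list and the adjusted estimator to an analysis plan, which is not shown here. All of this stands, and it makes the point a recommendation and not a correction.

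Entry is also restricted to moderate or high Braden risk and to low nutritional scores. That could narrow the spread of baseline risk and push R² towards the low end of the range. This stands too.

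One qualification: the article leads with a per-protocol analysis, and randomisation does not fully protect that set. Adjustment would help there only for measured factors, and the article gives no basis for sizing the effect. It is not counted in the figures.

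What survives is narrower. The article does describe both a primary contrast and a multivariate analysis, and it does not connect the second to the margin that decides the trial.

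**Conclusion.** The point holds as an optional improvement in efficiency. At the plan's own one-sided 5% and 306 evaluable patients per arm, the gain is about 2 to 7 percentage points of power for an assumed R² of 0.05 to 0.20, and nil if R² is near zero. The figures rest on a 45% risk in both arms and no true difference, as the plan assumes.

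A reader might infer more, but the article does not support these stronger readings:
- **That the logistic model cannot serve the margin.** Only the raw odds ratio is off the scale; the fitted model can be standardised to a risk difference. Nowhere does the article say that an odds ratio will decide noninferiority.
- **That the baseline data are wasted, or that the Braden score is excluded.** Some baseline variables enter the multivariate and survival analyses, and the Discussion's list of adjustment variables is given as examples only.
- **That the lost precision matters because true power is about 70%.** That figure (70.1%) arises if the 95% interval is two-sided while the sample size uses one-sided 5%. It is a separate matter and should be judged separately.

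**What to change.** Prespecify the covariate-standardised (marginal) risk difference, olive oil minus HOFA, as the primary estimate:
- Fit the planned logistic model with treatment, baseline Braden score, nutritional score, previous ulcer, age and sex.
- Average the predicted risks over all analysed patients, once under each treatment, and take the difference.
- Obtain its confidence interval by the delta method or bootstrap. Compare the upper limit with 10 points, since a larger difference means more ulcers under olive oil.
- Report the crude difference as a sensitivity analysis, and state that the standardised difference decides noninferiority.

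At the planned risk there would be about 0.45 × 612 ≈ 275 events, ample for six model terms.

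The cost is a few sentences in the analysis plan and a little extra programming. The covariates must be fixed before unblinding; the Trial status section says that enrolment and follow-up were still under way. No new data and no change in sample size are needed.

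### The Welch and Brown-Forsythe tests are tied to equal variances, the reverse of their purpose; a minor error confined to the secondary bivariate analyses

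*Protocol article*

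**What the plan says.** The relevant rules are in one paragraph of the Statistical analysis section of the protocol article.

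- For quantitative outcomes across categories, "analysis of variance (ANOVA) will be applied for the association of quantitative and qualitative variables in the necessary cases". The same sentence adds "robust measures of central tendency in cases of homoscedasticity", with Levene's test as the check, "by means of the Welch and Brown-Forsythe test".
- The preceding sentences cover Student's t and "chi-squared tests according to the characteristics of the variables analyzed in the event that these are normally distributed". They continue: "Otherwise, nonparametric tests will be applied, such as the Wilcoxon and Man-Whitney U tests".

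The abstract lists most of these tests without conditions. No other section corrects or restates the variance rule. The primary comparison is described separately, as effect measures "with their respective confidence intervals at 95" per cent, read against delta.

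**The concern.** Classical ANOVA assumes a common variance. The Welch and Brown-Forsythe procedures drop that assumption, so an analyst turns to them when Levene's test signals unequal variances. The article attaches them to the opposite finding. Followed literally, they are used where they are not needed, and the classical test is left by implication where its error rate can be wrong.

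This is more than detail an article may leave to a full plan: a condition is stated, and it is reversed. An analyst must either apply it or depart from the published text. At stake is the reliability of secondary p-values from comparisons of unequal groups. If the smaller group is the more variable, the classical test finds too many differences. If the larger group is, it finds too few.

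The sentence on t and chi-squared has a related weakness. Its grammar puts chi-squared under a normality condition that a test on categorical counts does not have.

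**Working it through.** **Inputs from the article (Sample selection).** Noninferiority test on proportions, one-sided 5%, power 80%, 45% in each arm, delta 10%, 306 per arm (612), 15% withdrawal, 360 per arm (720).

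**The plan's own figure.** n = (1.645 + 0.842)² × 2 × 0.45 × 0.55 / 0.10² = 6.18 × 0.495 / 0.01 ≈ 306 per arm (307 if rounded up), and 306 / 0.85 = 360. The sample size reproduces and does not depend on the point raised here. It implies 720 − 612 = 108 withdrawals.

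**Assumed.** All standard deviations and all subgroup sizes other than 612 and 108. Data are normal with equal means, and tests are at two-sided 5%.

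**1. Three groups, where the ANOVA sentence applies directly.** Simulated type I error, groups of 300, 200 and 100:

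| SDs | Classical ANOVA | Welch |
|---|---|---|
| 1, 1, 2 | about 14% | about 5% |
| 2, 1, 1 | about 2% | about 5% |

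A second simulation included the Levene step and used groups of 400, 150 and 62. With SDs 1, 1.5, 2 the rule as written gave 18.5%, and with SDs 2, 1.5, 1 it gave 1.2%. With the condition turned round, both became 5.1%.

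**2. Two groups, only if the rule is also taken to govern the t test.** Let n₁ = 612 with SD 1 and n₂ = 108 with SD r.

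- Pooled variance: V = (611 + 107r²) / 718.
- SE used by the classical test: √[V(1/612 + 1/108)].
- True SE: √(1/612 + r²/108).
- Type I error: 2[1 − Φ(1.96 × SE used / true SE)].

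| r | V | SE used | True SE | Type I error |
|---|---|---|---|---|
| 1.25 | 1.084 | 0.109 | 0.127 | about 9% |
| 1.5 | 1.186 | 0.114 | 0.150 | about 14% |
| 2 | 1.447 | 0.126 | 0.197 | about 21% |

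If the larger group has twice the SD instead, the result is about 0.2%.

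**3. Equal arms.** With n per arm, the pooled variance is (s₁² + s₂²)/2. The classical SE² is then (s₁² + s₂²)/2 × 2/n = (s₁² + s₂²)/n, which is the Welch SE². Simulation at 306 against 306 with SDs 1 and 2 gave 5.0% under either rule.

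**4. Equal variances.** With 400, 150 and 62, SD 1 throughout and means 0, 0.2 and 0.4, power was 84.6% for classical ANOVA and 84.0% for Welch. Using Welch when it is not needed costs almost nothing. The harm comes from not using it when it is needed.

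**5. Chi-squared against the rank test.** On an assumed 2×2 table (138/306 against 110/306), chi-squared gives p = 0.0211 and Mann-Whitney p = 0.0212, practically the same. On an assumed table with three unordered categories (150, 36, 120 against 120, 96, 90), chi-squared gives p = 2.7 × 10⁻⁸. Mann-Whitney then runs from about 2 × 10⁻⁶ to 0.82, depending only on the arbitrary order of the categories. A literal reading would matter for such variables but hardly for binary ones.

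**The case against.** The reversed word itself is hard to defend. It may be a translation slip, but nothing in the article shows that, and a likely slip still needs correcting. The objections to its reach are stronger, and most of them stand.

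- **The clause belongs to the ANOVA sentence.** Student's t is named earlier, with no variance condition. The two-group figures therefore follow only if the rule is extended to the t test.
- **That classical ANOVA stands under unequal variances is inferred.** The article presents the robust tests as an addition to ANOVA and names nothing for unequal variances. The inference is reasonable but not stated.
- **The link to attrition and refusal is not in the text.** A reader might infer that the comparisons of participants with refusers, and of withdrawals with completers, are exposed to an error of about 21%. The Discussion says only that differences will be taken into account and that "The same procedure will be applied for withdrawals during the follow-up period". It names no test and gives no number of refusals. The 21% also needs a doubled SD in the smaller group, which is an assumption.
- **The chi-squared sentence has a sensible reading.** A reader might infer that chi-squared would be dropped for any variable that is not normal. The wording "according to the characteristics of the variables analyzed in the event that these are normally distributed" also allows a choice by variable type, with normality relevant only to quantitative variables. This is ambiguity rather than a clear wrong rule.

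**Conclusion.** The variance condition is wrong as written, and nothing else in the article corrects it. The point is minor and concerns secondary bivariate analyses only.

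Its size depends on assumed SDs and group sizes. Under the three-group settings of 300, 200 and 100, type I error is about 14% or 2% in place of 5%. If the rule is extended to two groups of 612 and 108, it is about 9% to 21% as the smaller group's SD goes from 1.25 to 2 times the larger group's. Where either the group sizes or the variances are equal, little or nothing changes.

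A reader might also infer that the noninferiority conclusion is at risk. It is not: that decision rests on a confidence interval set against delta and uses none of these tests.

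**What to change.** - Replace homoscedasticity with heteroscedasticity in the ANOVA sentence, and state that the same rule covers two-group comparisons through Welch's t test.
- Reword the sentence on t and chi-squared so that the normality condition and the rank-test fallback apply to quantitative variables only, with chi-squared for categorical variables.

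The cost is a change of wording in one paragraph. No data collection, sample size or primary analysis is touched. The article describes the trial as still enrolling and following patients, so the correction can be made before analysis.

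### Ulcer incidence read from the secondary Kaplan-Meier curves will exceed the proportion who develop an ulcer, because by default these curves censor patients who die ulcer-free

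*Protocol article*

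**What the plan says.** The Statistical analysis section of the protocol article plans a time-to-ulcer analysis: "An analysis according to the Kaplan-Meier curves and log-rank test will be carried out to determine the progress of the appearance of pressure ulcers". The same sentence then names the factors by which the curves are to be compared, with the words "taking into account the treatment applied, the sex, age, nutritional status, and functional degree of the patient"; how old the caregiver is completes the list.

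This is not the main analysis. The main outcome is the incidence of grade 2 ulcers over 16 weeks (112 days). It is analysed by risk difference, number needed to treat, relative risk and relative risk reduction with 95% confidence intervals, judged against the 10-point margin. The cost-effectiveness analysis also takes ulcer incidence as a percentage.

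On who leaves early, the Sample selection section says "Taking into account that the expected withdrawal rate is 15.00" per cent, without dividing that figure by cause. The exclusion criteria remove terminally ill patients. Weekly assessment runs until the end of follow-up or the first ulcer. Death during follow-up is not mentioned anywhere in the article, either as a reason for censoring or as a competing event.

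**The concern.** The stated purpose of the curves is to show how ulcers appear over time, which is a question about cumulative incidence. Kaplan-Meier answers that question only if a censored patient keeps the same future ulcer risk as those still under observation. A patient who has died cannot develop an ulcer. If that death is censored in the usual way, 1 minus Kaplan-Meier estimates the ulcer risk in a hypothetical setting without death, and it lies above the proportion of patients who actually develop an ulcer.

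Deaths are foreseeable here. Participants are immobilized, at moderate or high risk on the Braden scale, and score 10 or less on the nutritional scale, and the article describes pressure ulcers as mainly affecting older people. Follow-up is 112 days, against 7 to 30 days in the earlier trials that the article cites.

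What is at stake is how the curves are read. Their height at week 16 could be taken as the ulcer incidence and set beside the crude proportion from the main analysis, which measures something else. Curves for strata with different mortality would also be raised by different amounts.

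**Working it through.** **The plan's own figures.** The inputs, all from Sample selection, are: "assuming that the proportion in the reference (control) group is 45.00% and the proportion in the experimental group is 45.00" per cent, "the noninferiority bound (delta) is 10.00" per cent, "the level of statistical significance is 5.00" per cent with "unilateral proportions for two independent samples" (one-sided), and "To achieve a power rate of 80.00" per cent.

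n per arm = 2 × 0.45 × 0.55 × (1.645 + 0.842)² / 0.10² = 306.04, against the stated 306. With 15% withdrawals, 306 / 0.85 = 360, as stated. The sample size reproduces, so 45% and 360 per arm are used below.

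**Model.** Assume constant ulcer and death hazards over the 112 days. Let *c* be the true cumulative incidence of ulcer and *d* the proportion dying ulcer-free.

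- Total cumulative hazard: H = −ln(1 − c − d).
- Ulcer share: H₁ = H × c / (c + d).
- What Kaplan-Meier shows with deaths censored: 1 − exp(−H₁).

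Worked case, c = 0.45 and d = 0.05: H = −ln(0.50) = 0.6931; H₁ = 0.6931 × 0.45 / 0.50 = 0.6238; 1 − exp(−0.6238) = 0.4641. The excess is 1.4 points.

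**Range.** The document gives no value for *d*. The range below goes up to the case in which every one of the 15% expected withdrawals is a death. The standard error (SE) of one arm's incidence is √(0.45 × 0.55 / 360) = 2.62 points.

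| Ulcer-free deaths (assumed) | 1 − KM at true 45% | Excess, points | Excess / SE | Excess at true 20% (assumed) | Excess at true 10% (assumed) |
|---|---|---|---|---|---|
| 2% | 45.5% | 0.5 | 0.2 | 0.2 | 0.1 |
| 5% | 46.4% | 1.4 | 0.5 | 0.6 | 0.3 |
| 10% | 48.0% | 3.0 | 1.1 | 1.2 | 0.6 |
| 15% | 49.7% | 4.7 | 1.8 | 1.8 | 0.9 |

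**Subgroups with the same ulcer hazard.** Set 1 − KM = 45% in both, so H₁ = −ln(0.55) = 0.5978. Let D be the risk of death in the absence of ulcers, with H₂ = −ln(1 − D). The true incidence is H₁ / (H₁ + H₂) × [1 − exp(−(H₁ + H₂))].

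- D = 3%: 0.5978 / 0.6283 × (1 − 0.5335) = 44.4%, overstated by 0.6 point.
- D = 15%: 0.5978 / 0.7604 × (1 − 0.4675) = 41.9%, overstated by 3.1 points.

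The two curves coincide, although the proportions developing an ulcer differ by 2.5 points.

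**Subgroups with the same true incidence.** With c = 45% in both and ulcer-free deaths of 2.5% and 12.5%, the curves reach 45.7% and 48.8%, a gap of 3.1 points. The ulcer cumulative hazards are 0.610 and 0.670, a ratio of about 1.10.

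**Treatment contrast.** With equal ulcer and death hazards in the two arms, both curves rise by the same amount and the difference stays at 0. A true 50% against 40% reads as 10.2 to 10.6 points when the risk of death in the absence of ulcers is 5% to 15% in both arms.

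**The case against.** The strongest reply is that nothing important depends on these curves. The noninferiority test, its confidence interval and the cost model all rest on proportions, and the article does not promise a 16-week incidence read from a Kaplan-Meier curve. That stands, and it makes the point minor. A reader might infer that the trial's 16-week ulcer incidence will be overstated. The document does not support this: only incidence read from the secondary curves is affected.

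Second, the article states no censoring rule, and a condensed article may leave that to a fuller document. It would be too strong to say that the method can only censor deaths. Keeping ulcer-free deaths in the risk set to day 112 would give the cumulative incidence if there were no other censoring. Still, the estimator and its purpose are named, and its ordinary form censors deaths.

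Third, the hazard is a defensible quantity for a preventive product applied to living patients, and the log-rank test compares it validly. A reader might infer that the 3.1-point gap between subgroups with equal incidence is an artefact. It is not: under the model it reflects a real hazard ratio of about 1.10, and equal hazards would give no gap at any mortality. It misleads only if read as a difference in incidence. It is also modest against sampling error: with all 720 patients split evenly, the SE of the difference is √(2 × 0.45 × 0.55 / 360) = 3.7 points, so the gap is about 0.8 SE.

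Fourth, mortality is unknown, terminally ill patients are excluded, and nutritional status is restricted at entry, which narrows that contrast. All of this stands, so the size can be given only as a range.

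**Conclusion.** The point holds as a minor one about a secondary analysis. If ulcer-free deaths are censored in the usual way, the direction of the error is certain: incidence read from the curves exceeds the proportion who develop an ulcer. Its size is conditional. At the plan's 45% it runs from about 0.5 point with 2% ulcer-free deaths to 4.7 points with 15%. With ulcer incidence near 10% it stays below 1 point. These figures rest on constant hazards and on assumed death rates.

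The excess is larger wherever mortality is higher. That this applies to the older and frailer strata is plausible, but it is an assumption, since the article gives no mortality by stratum. A reader might also infer that the comparison of olive oil with HOFA is distorted. With similar deaths in the two arms it is essentially unaffected, and nothing in the document suggests that deaths will differ by arm.

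**What to change.** In the Statistical analysis section:

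- Present Aalen-Johansen cumulative incidence curves of the first grade 2 ulcer, by arm and by the listed characteristics, with death before an ulcer as a competing event.
- Censor only patients who leave alive and ulcer-free, or who reach day 112 without an ulcer.
- Record the date of death, so that death can be separated from other reasons for leaving.
- Keep the log-rank test, labelled as a comparison of the cause-specific ulcer hazard. Gray's test may be added to compare cumulative incidence, but it is optional.

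The cost is a change of analysis wording and one recorded date, with no added patients or visits and no change to the main analysis. The reported incidence will be slightly lower than the Kaplan-Meier figure, and the curves may need software other than the package named in the plan. If deaths prove rare, the two sets of curves will nearly coincide and nothing is lost.
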